#### Post-intervention evaluation session

Following the 4-week intervention period, participants will complete a post-intervention evaluation session identical to the pre-intervention session. This assessment will include clinical outcomes related to mental health and cognition, neural and physiological biomarkers (functional and structural MRI, physiological data), and burden ratings.

#### Follow-up evaluation session

Three months after completing the intervention, participants will complete a final follow-up evaluation session. This session will assess only behavioral clinical outcomes related to mental health and cognition; no biomarkers will be collected.

### Outcome measures

This study is a clinical trial assessing the feasibility of an IML, and therefore the primary outcomes will focus on feasibility metrics. Primary outcomes will include retention and adherence, feasibility, acceptability, fidelity, and burden. Secondary outcomes will include recruitment and randomization. Table 2 provides a detailed description of each outcome along with predefined benchmarks for success.

### Statistical analysis

The primary and secondary outcomes of intervention feasibility will be reported using percentages (see Table 2, benchmarks for success). One-sided exact binomial tests and proportional z-tests will be used to assess whether the outcomes have success rates above the benchmarks. Success rates will be compared between the treatment group and control group using Chi-squared tests or Fisher’s Exact Tests if non-normality presents. We will identify potential factors that are associated with the feasibility outcomes, which will help refine the design of a large-scale clinical trial.

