### Procedures and assessments

#### Screening

Eligibility will be assessed using a well-characterized stroke registry. Initial screening will verify age and confirm a diagnosis of ischemic or hemorrhagic stroke occurring at least six months prior to enrollment. Additional exclusion criteria will then be reviewed. If data for key screening measures are missing from the registry, a study team member will contact the patient to explain the study and gauge interest. If the patient agrees to participate, they will complete a screening session (online or in person) to confirm eligibility. This session may include: (1) the Hearing Handicap Inventory for the Elderly – Screening version (HHIE-S; Ventry & Weinstein, 1982), a 10-item self-report measure of hearing loss validated against pure-tone audiometry (Lichtenstein et al., 1988); (2) the Montreal Cognitive Assessment (MoCA), a standardized screening tool used to detect cognitive impairment and early signs of dementia (Nasreddine et al., 2005). The MoCA assesses multiple cognitive domains, including executive function (e.g., trail-making), visuospatial abilities (e.g., clock-drawing), attention (e.g., digit span), language (e.g., sentence repetition and verbal fluency), abstraction (e.g., identifying similarities between two concepts), short-term memory (via a delayed recall task), and orientation (e.g., stating the current date, month, and year); (3) the Montreal Battery of Evaluation of Amusia (MBEA; Peretz et al., 2003), assessing the presence of amusia, a disorder affecting pitch and melody perception. Participants hear pairs of short melodies and judge whether they are the same or different, across separate pitch and rhythm discrimination tests; (4) the extended Barcelona Music Reward Questionnaire (eBMRQ; Mas-Herrero et al., 2013; Cardona et al., 2022), a 24-item self-report questionnaire that assesses individual differences in sensitivity to music-related reward. The eBMRQ includes subscales for musical seeking, emotion evocation, mood regulation, social reward, sensory-motor, and music absorption. To screen for specific musical anhedonia, only the original BMRQ score (excluding the music absorption items) will be used; and (5) an MRI safety screening questionnaire assessing eligibility criteria for neuroimaging (see Supplementary Materials). If the patient meets all eligibility criteria, they will be enrolled in the study, randomized to either the IML or control group using a computer-generated randomization sequence, and scheduled for a baseline evaluation session. Experimenters will not be blinded to group allocation.

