#### Pre-intervention period

After the baseline assessment, participants will undergo a 4-week no-intervention period to assess the stability of outcome measures. During this time, they will use the provided iPad to complete daily Ecological Momentary Assessments (EMAs), which will track mental health status and collect additional control measures. EMAs will be administered through the mEMA app (https://ilumivu.com/solutions/ecological-momentary-assessment-app/), with participants receiving daily notifications prompting them to complete a brief survey within a six-hour window (6:00 p.m. to midnight). Two surveys will be administered through the mEMA app during the 4-week pre-intervention period: (1) the first is a daily survey assessing control variables related to the four mechanistic pathways through which enriched environments are thought to promote brain plasticity and recovery: motor, sensory, cognitive, and social stimulation (Vive et al., 2022). This survey uses Likert scales to measure the extent of motor, sensory, cognitive, and social activity throughout the day, as well as music engagement. Specifically, whether participants listened to music outside of scheduled sessions and whether the listening was intentional (see Supplementary Materials). Participants will complete this survey each weekday starting after the baseline session; and (2) the Profile of Mood States (POMS), a 36-item standardized self-report questionnaire that assesses temporary mood states across six subscales: Tension-Anxiety, Depression-Dejection, Anger-Hostility, Vigor-Activity, Fatigue-Inertia, and Confusion-Bewilderment (McNair et al., 1971). The POMS will be administered every three days beginning on the first day of the 4-week period (i.e., days 1, 4, 7, 10, 13, 16, 19, 22, 25 and 28, for a total of 10 data points).

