**Feasibility Measures**							
Burden Ratings (Patients)		X		X		X	X
Acceptability Ratings (Patients)					X		
Feasibility Ratings (Team Member)					X		
Fidelity Ratings (Team Member)					X		

**Table 2. T2:** Outcome measures and benchmarks for success.

Outcome	Description	Benchmark for success
Recruitment	Number of enrolled participants per month	At least 2 per month
Randomization	Proportion of screened patients who are enrolled Proportion of enrolled patients who complete the baseline and pre-intervention evaluations and attend at least one IML/Audiobook session	At least 30% At least 80%
Retention and Adherence	Proportion of enrolled and randomized participants who complete the IML/Audiobook sessions	At least 80% of randomized patients complete at least 80% of the IML/Audiobook sessions
Feasibility	Proportion of listening sessions considered fully feasible; the team member making the phone call will rate the session as “not feasible” , “partially feasible” or “fully feasible”	At least 80% of all sessions considered as fully feasible
Fidelity	Proportion of listening sessions delivered according to the protocol; video calls with patients will be recorded and a team member who was not present during the call will score the session as “delivered according to protocol” or “not delivered according to protocol”	At least 80% of all sessions delivered according to the protocol
Burden	Proportion of planned evaluations that are completed at each time point (baseline, pre-intervention, post-intervention, follow-up) Burden rating: patients will rate each evaluation as “not burdensome” , “partially burdensome” , or “very burdensome”	80% of patients complete the evaluations at each time point At least 80% of patients rate evaluations at each time point as not burdensome
Patient acceptability	Acceptability ratings: patients will rate each listening session as “not acceptable” , “partially acceptable” or “fully acceptable” .	80% of listening sessions rated as fully acceptable

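### The post-intervention comparison of burden ratings between arms leaves out each participant's own rating of the identical pre-intervention visit

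*Protocol article*

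**What the plan says.** The Outcome measures section makes burden primary: "Primary outcomes will include retention and adherence, feasibility, acceptability, fidelity, and burden". Table 2 gives burden two parts. One is completion: "Proportion of planned evaluations that are completed at each time point (baseline, pre-intervention, post-intervention, follow-up"). The other is the rating, on a three-level scale, with the benchmark "At least 80% of patients rate evaluations at each time point as not burdensome".

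The Statistical analysis section plans two kinds of test. Against the benchmarks: "One-sided exact binomial tests and proportional z-tests will be used to assess whether the outcomes have success rates above the benchmarks". Between arms: "Success rates will be compared between the treatment group and control group using Chi-squared tests", with Fisher's exact test as the alternative. The second sentence excepts no outcome or visit and names no stratum or covariate.

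On timing, the Screening section has eligible patients "randomized to either the IML or control group using a computer-generated randomization sequence, and scheduled for a baseline evaluation session". After baseline, "participants will undergo a 4-week no-intervention period to assess the stability of outcome measures". The pre-intervention evaluation follows, with a burden rating at its end, and only then does the intervention start (Study Design). Afterwards, "participants will complete a post-intervention evaluation session identical to the pre-intervention session". The follow-up evaluation has no MRI or physiology.

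**The concern.** At the post-intervention visit the arms can differ because of four weeks of music or audiobooks. The participant has by then rated the same procedures (questionnaires, cognitive tests, scanner session) once, about four weeks earlier and before any session. How burdensome people find a long visit with a scan is likely to vary a good deal between persons for reasons unrelated to the arm. An unadjusted two-by-two test leaves that variation in the error term. With 30 per arm there is little power to spare.

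A second matter follows from reading the arm comparison together with Table 2. Burden success is defined at each of four visits, and two of these come before the first listening session. A difference between arms there cannot be burden caused by listening, and the plan does not say how it would be read.

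**Working it through.** **No figure to reproduce.** The protocol gives no alpha, power, effect size or dropout for the arm comparison, and it bases the sample size on earlier feasibility studies. What follows is an illustration.

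**Inputs**
- 30 per arm (Study population).
- 80% not burdensome in one arm (the Table 2 benchmark) and 60% in the other (assumed).
- Two-sided 5% (assumed; the protocol says one-sided only for the benchmark tests) and no dropout (assumed).
- Pre-intervention rate 80% in both arms (assumed).
- Pre/post correlation not given, so varied.

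**Step 1: unadjusted power.** With pooled rate 0.7:
- SE under no difference = √(2 × 0.7 × 0.3 / 30) = 0.1183.
- SE under the alternative = √((0.8 × 0.2 + 0.6 × 0.4) / 30) = 0.1155.
- Power = Φ((0.20 − 1.96 × 0.1183) / 0.1155) = Φ(−0.276) = 0.39.

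For 80% power, about 82 per arm would be needed.

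**Step 2: stratified test.** Form two strata from the participant's pre-intervention rating (not burdensome, yes or no). In each stratum let A be the successes in one arm, n₁ and n₀ the arm sizes, n their sum and m all successes. The Mantel-Haenszel statistic is

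Z = Σ(A − n₁m/n) / √Σ[n₁n₀m(n − m) / (n²(n − 1))].

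The outcome is still the yes/no success of Table 2. Pre and post ratings were simulated from a latent bivariate normal, 20,000 trials per row:

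| Latent correlation | Correlation of yes/no ratings | Unadjusted | Stratified | Change (points) |
|---|---|---|---|---|
| 0 | 0.00 | 0.392 | 0.389 | −0.3 |
| 0.5 | 0.30 | 0.391 | 0.416 | +2.5 |
| 0.7 | 0.46 | 0.392 | 0.464 | +7.2 |
| 0.9 | 0.69 | 0.393 | 0.589 | +19.6 |

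A separate set of runs gave stratified power of 0.38, 0.40, 0.43, 0.46 and 0.54 at latent correlation 0, 0.3, 0.5, 0.7 and 0.85, against 0.39 to 0.41 unadjusted. For 80% v 50%, power rises from about 0.69 to 0.72 at latent correlation 0.5 and to 0.77 at 0.7.

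**Step 3: type I error.** With 80% in both arms, the stratified test rejects in 4.5% to 5.0% of trials and the unadjusted test in 4.8% to 5.0%.

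**Step 4: the two visits before any session.** Two components at four visits make 2 × 4 = 8 comparisons if every visit is tested. Four of them (baseline and pre-intervention) precede the first session. At 30 per arm and a common rate of 80%, the exact size of one test is 4.9% (chi-squared) or 2.2% (Fisher).
- Two rating tests, if independent: 1 − 0.951² = 10% or 1 − 0.978² = 4%.
- All four tests, if independent: 1 − 0.951⁴ = 18% or 1 − 0.978⁴ = about 9%.

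The figures for four tests are upper extremes. If true completion at these visits is 95%, the exact size of one Fisher test is 0.0015, so the completion tests add almost nothing.

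**The case against.** **The sentence is general.** It does not spell out testing at each visit, and covariates are often left to an analysis plan. That stands for the visits: testing at each one is the natural reading of Table 2, not a stated rule. It does not remove the main point, because the protocol names the test, and that test is unadjusted.

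**The gain is uncertain.** This stands. The correlation is unknown, and at 0.5 or below the benefit is slight. A reader might credit the participant's own rating with a larger gain by comparing the yes/no chi-squared test with a stratified test of the three-level score. That mixes two changes. At latent correlation 0.5, power is 0.40 for chi-squared, 0.42 for an unstratified ordinal test and 0.44 for the stratified ordinal (van Elteren) test. At 0.3 the figures are 0.41, 0.43 and 0.42. The ordinal test also no longer compares the success rates that Table 2 defines.

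**The early visits may be informative.** A reader might infer that the baseline and pre-intervention comparisons carry no information and that the arms should be pooled there. The protocol does not support this. Randomization precedes baseline, the experimenters are not blinded, and the section on the music intervention places device training and playlist creation in the baseline session. Allocation could therefore affect early completion or ratings, and pooling would hide early differential dropout.

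**Not every later visit is identical.** Only post-intervention repeats the pre-intervention visit. At follow-up the pre-intervention rating is a covariate, not a rating of the same visit. Completion has no prior rating to adjust for.

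**The covariate is measured after randomization.** If knowing the allocation shifts the pre-intervention rating, adjustment removes that part of the difference. What remains is the change in burden since sessions began. Showing the crude rates by arm beside the adjusted result keeps both visible.

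**Conclusion.** The point holds for the burden rating at post-intervention. The named test ignores a measurement that the protocol already collects on an identical visit before any session. At 30 per arm and 80% v 60%, using it adds about 0 to 3 points of power at a latent correlation of 0.5 or below and about 7 to 14 points at 0.7 to 0.85, with type I error near 5%. If the ratings are unrelated, about one point is lost. These sizes rest on the assumed rates, a two-sided 5% level, no dropout and a pre-intervention rating unrelated to arm.

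The power remains low in either case (about 0.54 at correlation 0.85). The feasibility conclusion comes from the benchmark tests, which this does not touch. It is an inexpensive improvement, not a flaw that endangers the trial.

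For the two early visits, the supported conclusion is limited: a difference between arms there is not an effect of listening. An 18% risk of a false signal should not be quoted as expected, since it needs four independent tests and a true rate of 80% for completion as well.

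**What to change.** In the Statistical analysis section, add wording to this effect:

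- The post-intervention proportion rating the evaluation as not burdensome will be compared between arms by a Mantel-Haenszel test stratified by the participant's own pre-intervention rating (yes/no), with crude rates shown by arm. The same stratification may be used at follow-up, with a note that this visit has no MRI or physiology. An ordinal analysis of the three-level rating is optional and supplementary.
- Burden ratings and completion at baseline and pre-intervention will be described by arm, without pooling, and will not be interpreted as effects of the listening sessions.
- A participant without a pre-intervention rating will form a separate stratum, or another rule stated in advance will apply.

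Leave the 80% benchmarks and their one-sided tests as they are. The cost is a few sentences and no new data. If the benchmark is just met at pre-intervention, about 0.8 × 60 = 48 participants fall in one stratum and 12 in the other, so the second stratum is small. A finer split is not advisable.

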### Study population

We aim to enroll 60 participants (30 per group), aged 50 to 90, with a confirmed diagnosis of ischemic or hemorrhagic stroke occurring at least six months prior to enrollment. The sample size was informed by previous feasibility studies of complementary health interventions (Richard-Lalonde et al., 2023; Doorley et al., 2022; Portz et al., 2023; Smith et al., 2022). Participants will be excluded if they meet any of the following criteria: (1) significant hearing loss, defined by a score >26 on the Hearing Handicap Inventory for the Elderly Screening (HHIE-S; Ventry and Weinstein, 1982); (2) contraindications for MRI; (3) cognitive impairment that may interfere with completion of study procedures, defined as a Montreal Cognitive Assessment (MoCA; Nasreddine et al., 2005) score below 22 (unless the lower score is attributable to expressive aphasia); (4) specific musical anhedonia, defined as a score below 60 on the Barcelona Music Reward Questionnaire (BMRQ; Mas-Herrero et al., 2013); or (5) amusia, defined as a score below 70% on the Montreal Battery of Evaluation of Amusia (MBEA; Peretz et al., 2003). Participants will not be excluded if they are currently taking medications that may affect brain function (e.g., antidepressants) or if they are engaged in other complementary therapies (e.g., mindfulness, yoga). However, they will be instructed not to initiate any new medications or therapies during the study period. Participants who begin a new treatment during the study will be excluded from the analysis. Participants will also be discontinued from the study upon their request or if there is a worsening of their medical condition that compromises safety or study participation.

Eligible patients will be contacted by phone, and the study will be explained using a standardized script. Patients who do not make an immediate decision (e.g., need time to consider participation) will receive up to two follow-up contacts via phone or email over a two-week period. To meet recruitment targets, we aim to enroll at least five participants per month over the course of 12 months.

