A strength of this study is access to a large, diverse, and well-characterized population of chronic stroke patients from the greater New York City area. Another strength of the study is the use of multimodal methods to assess intervention effects across behavioral, physiological, and neuroimaging (MRI) domains, providing a more comprehensive understanding of the intervention’s impact. However, the study has limitations. It is not powered to detect clinical changes in mental health, cognition, or neuroplasticity, as its primary goal is to assess feasibility. Additionally, as a single-center study, generalizability to other clinical settings or populations may be limited.Regardless of the outcomes of the proposed work, we believe this study will help advance the field of music-based interventions at the theoretical, experimental, and clinical level. The IML intervention tested here may also be adaptable to other aging-related neurological conditions, such as Alzheimer’s disease and other dementias, broadening its potential public health impact.

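### The arms are compared on feasibility outcomes only by significance tests, which at 30 per arm say little; report the difference with a 95% interval instead

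*Protocol article*

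**What the plan says.** The Statistical analysis section of the protocol article gives three elements for the feasibility outcomes.

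- Reporting: "The primary and secondary outcomes of intervention feasibility will be reported using percentages".
- Against the benchmarks: "One-sided exact binomial tests and proportional z-tests will be used to assess whether the outcomes have success rates above the benchmarks".
- Between the arms: "Success rates will be compared between the treatment group and control group using Chi-squared tests", or Fisher's exact tests.

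The third element is the subject here. No significance level, estimate of the difference, interval or precision target is attached to it.

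The Study population section sets 30 patients per group, and the basis is precedent: "The sample size was informed by previous feasibility studies of complementary health interventions". The Discussion says of the study "It is not powered to detect clinical changes in mental health, cognition, or neuroplasticity". That covers the clinical and neural outcomes and is silent on the between-arm feasibility comparison.

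Table 2 has outcomes with two kinds of unit. Some count patients, for example "At least 80% of randomized patients complete at least 80% of the IML/Audiobook sessions". Others count sessions, for example "At least 80% of all sessions considered as fully feasible".

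**The concern.** The trial is run to inform a larger one, and the audiobook arm is the intended control. Whether patients stay with audiobooks as well as with music is therefore something the next design team needs to know, because unequal adherence or completion can bias a later efficacy comparison. The Introduction itself describes adherence and retention as a problem in this field, citing a study with 24% dropout and 22.2% adherence.

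A test of no difference is a weak tool for that question at this size. It gives a p-value, which shows neither how large the gap is nor how large it could still be. If the test seldom rejects when the arms truly differ by 10 to 20 points, a non-significant result leaves the designer where they started.

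**Working it through.** **Inputs**

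- n = 30 per arm (Study population).
- Reference rate 80%, the patient-level benchmark in Table 2. Rates of 50%, 60%, 70% and 90% are assumed for comparison.
- Two-sided level 0.05, assumed because the article states none.

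The sample size of 60 comes from precedent, so there is no power calculation to reproduce. The accrual figure is consistent with it: 5 per month x 12 months = 60.

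**Step 1. Power of the stated tests**

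All 31 x 31 pairs of counts were enumerated. Power is the total binomial probability of the pairs with p at or below 0.05, using the uncorrected chi-squared test and Fisher's exact test.

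| True rates | Chi-squared | Fisher |
|---|---|---|
| 80% v 70% | 0.14 | 0.09 |
| 80% v 60% | 0.39 | 0.30 |
| 80% v 50% | 0.69 | 0.60 |
| 80% v 90% | 0.19 | 0.10 |
| 90% v 70% | 0.50 | 0.37 |

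Hand check by the normal approximation for 80% v 70%:

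- Pooled rate 0.75, so the null SE is sqrt(2 x 0.75 x 0.25/30) = 0.1118.
- The SE under the alternative is sqrt((0.8 x 0.2 + 0.7 x 0.3)/30) = 0.1111.
- Power = Phi((0.10 - 1.96 x 0.1118)/0.1111) = Phi(-1.07) = 0.14.

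A true 20-point gap (80% v 60%) is missed with probability 1 - 0.39 = 0.61 (chi-squared) or 1 - 0.30 = 0.70 (Fisher). Starting from 80%, power of 80% needs the other arm to fall to about 45% (chi-squared) or 42% (Fisher), a gap of 35 to 38 points. Detecting 80% v 70% with 80% power would need 294 per arm, and 80% v 60% would need 82.

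**Step 2. What an interval would show**

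The Newcombe interval combines the Wilson limits (l, u) of each arm. With d = p1 - p2:

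- lower = d - sqrt((p1 - l1)^2 + (u2 - p2)^2)
- upper = d + sqrt((u1 - p1)^2 + (p2 - l2)^2)

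The Wilson limits are 0.627 to 0.905 for 24/30 and 0.423 to 0.754 for 18/30.

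- 24/30 v 24/30: 0 +/- sqrt(0.173^2 + 0.105^2) = 0 +/- 0.202.
- 24/30 v 18/30, lower: 0.20 - sqrt(0.173^2 + 0.154^2) = -0.03.
- 24/30 v 18/30, upper: 0.20 + sqrt(0.105^2 + 0.177^2) = 0.41.

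| Observed | Difference, points (95% interval) | Chi-squared p | Fisher p |
|---|---|---|---|
| 24/30 v 24/30 | 0 (-20 to +20) | 1.00 | 1.00 |
| 27/30 v 24/30 | +10 (-9 to +29) | 0.28 | 0.47 |
| 24/30 v 21/30 | +10 (-12 to +31) | 0.37 | 0.55 |
| 24/30 v 18/30 | +20 (-3 to +41) | 0.09 | 0.16 |

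All four results are non-significant, yet each is compatible with a gap of 20 points or more.

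**Step 3. Could the interval be used to declare the arms comparable?**

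Suppose the rule were that the whole 95% Newcombe interval must lie inside a margin fixed in advance. The probability of meeting it when the arms are truly identical is:

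| Margin | Both arms 80% | Both arms 90% |
|---|---|---|
| 10 points | 0 | 0 |
| 15 points | <0.001 | 0.02 |
| 20 points | 0.06 | 0.35 |
| 25 points | 0.39 | 0.70 |

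For any margin up to 20 points the rule would usually fail with identical arms. The interval is useful here for description, not for a formal claim of similarity.

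**Step 4. Scope**

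Steps 1 to 3 treat each patient as one observation. Feasibility, fidelity and acceptability are counted per session, up to 20 x 30 = 600 per arm from 30 patients. The figures above do not carry over to these outcomes, and a test or interval that treats the 600 sessions as independent would be wrong for them.

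**The case against.** The strongest reply is that nothing decisive hangs on this test. The primary objective is judged against the Table 2 benchmarks by separate one-sided tests, and the between-arm sentence is supplementary. That stands, and it limits the weight of the point.

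A reader might infer that the plan intends to treat a non-significant result as proof that audiobooks are a comparable control. The article does not say so. It says only that success rates will be compared, and its statement that the groups are matched for treatment intensity describes a common delivery protocol, not a conclusion drawn from a p-value.

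A reader might also infer that the plan hides how far apart the arms are. It does not: percentages are reported, so for patient-level outcomes the observed gap can be read off. What is missing is its uncertainty.

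Finally, interval reporting is often left to a full protocol or SAP, neither of which is shown, and naming a test does not rule out an interval. The reply is partly fair. But the article does fix the method of comparison, and the method it fixes is a poor one for arms of 30. The point concerns that choice, not a missing detail.

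**Conclusion.** The concern holds in a limited form. Significance tests are the only between-arm method the article states, and at 30 per arm they detect a 10-point shortfall from 80% with probability 0.14 or less and a 20-point shortfall with 0.39 or less. A non-significant result would leave gaps of 20 to 40 points open. This rests on an assumed two-sided 5% level, assumed reference rates and full enrolment with every patient counted; the conclusion is the same across the rates shown for gaps of 10 to 20 points. It applies to patient-level outcomes.

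The documents contain no wrong figure or contradiction on this point, and no stated decision changes. It is a cheap improvement to a supplementary analysis whose result the next trial will want.

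**What to change.** Amend the between-arm sentence in the Statistical analysis section as follows.

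- For each patient-level outcome (retention and adherence, completion of evaluations, burden rating), report the difference between arms with a 95% Newcombe interval as the main comparison.
- For session-level outcomes (feasibility, fidelity, acceptability), report the difference with an interval that allows for clustering of sessions within patients.
- Make the chi-squared and Fisher tests secondary or drop them, and state that no p-value will be used to conclude that the arms are alike.
- Do not add a rule that declares the arms comparable when the interval lies inside a fixed margin; Step 3 shows that this sample size cannot support one for margins up to about 20 points.

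The cost is a sentence or two, with no change to data collection or sample size. The drawback is that the patient-level intervals will be wide, about 20 points either way. That is an honest statement of what 30 per arm can show.
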